## Abstract

**Introduction and objectives::**

Mandible reconstruction with vascularized fibula flap is the standard treatment for segmental mandibulectomy in patients with tumor or trauma. But the height of the fibula graft is insufficient for dental implant placement and prosthetic rehabilitation to replace the missing teeth, which in turn will compromise the functional efficiency and aesthetics of the patient. Although the bone height can be augmented through onlay grafting with iliac crest, it is associated with limitations like donor site morbidity and fast resorbability. This suggests the need for a synthetic biomaterial for vertical bone augmentation in implant dentistry.

We have developed a biomimetic, porous, mechanically stable, and biodegradable nanocomposite named “NANOTEX BONE Graft” and its bone regeneration potential was evaluated in pre-clinical animal models. In this clinical trial, the safety as well as the efficacy of NANOTEX to augment new bone over fibula and further its ability to integrate with dental implants will be studied. The study has received the approval of the Ethics Committee of Amrita Institute of Medical Sciences and Central Drugs Standard Control Organization (CDSCO), India.

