Vascularised free fibula is the standard autograft used for mandibular reconstruction. Further, Titanium dental implants will be placed to the fibula for dental rehabilitation as it serves as an artificial analog of the missing teeth. This in turn enhances the quality of the patient’s life by improving the masticatory efficiency and aesthetic outcome [7]. Nevertheless, there is a height discrepancy between the native mandible and transplanted fibula, restricting the placement of dental implants [8]. The compromised implant length due to reduced vertical bone height can lead to an improper implant crown root ratio. In addition, an increased prosthetic height to achieve the occlusal plane level will lead to implant overloading and failure of the prosthesis. This necessitates the need for vertical bone augmentation in the fibula reconstructed mandible. Surgical techniques like double-barrelling and vertical distraction osteogenesis can increase bone height, but those techniques are complicated [9]. Onlay grafting using iliac crest (placement of graft on the fibula and its fixation with screws) is another option, but it has drawbacks such as high resorption rate and donor site morbidity [10]. Hence, there is a need for an efficient biomaterial to be placed over fibula, which can promote bone regeneration and increase the bone height. An ideal biomaterial should provide an extracellular matrix microenvironment that mimics the natural bone in regulating cell and tissue behavior. In load-bearing regions like mandible, the strength of the scaffold is also significant in providing signals for bone remodeling. This material also has to accept titanium implant placement. At present, there is no synthetic block graft available for intra-oral bone augmentation purposes to satisfy all these needs.

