### 1.3. Study Objectives

The primary objective of this study is to evaluate the safety of the NANOTEX BONE Graft in combination with the fibula flap implanted at segmental mandibulectomy defects. The secondary objective is to evaluate the efficacy of the NANOTEX BONE Graft in bone regeneration when augmented on the fibula and Titanium dental implant integration.

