### 2.8. Study procedure and data collection

*NANOTEX BONE graft augmentation on fibula*: A patient who is undergoing segmental mandibulectomy due to benign tumor or trauma will be included in the study after obtaining the consent. Pre-operative planning of the surgery includes virtual surgical planning and model surgery to determine the most ideal position of the fibula and NANOTEX BONE graft. Further, the mandible will be resected followed by free fibula flap reconstruction, which will be stabilized using plates and screws and anastomosed with host vessels as per standard protocol. Further, the height of the fibula will be augmented by placing the scaffold over the fibula and fix with screws and a plate. The size of the block graft will vary depending on the size of the patient defect and fibula. The skin paddle of the fibula flap will be inset to close the mucosal defect over the scaffold and fibula. Post-operative care will be taken as per standard clinical practice for fibula reconstruction.*Implant placement and Prosthetic rehabilitation*: The procedure for implant placement involves reconstructed site preparation and implant insertion. The number and size of titanium dental implants will be planned based on bone gain. The loading of the implant (prosthesis placement) will be done if the implant is integrated well with the bone.

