#### Secondary outcome

*Efficacy of NANOTEX BONE graft in supporting Bone Regeneration*: Bone regeneration will be assessed by Cone beam computed tomography (CBCT) assisted by virtual surgical planning and 3D reconstructed stereolithographic models. The radiographic linear measurements will be repeated in the models at each timeline for accuracy and measured in terms of bone height, bone density, bone union, and bone volume during the follow-up scan and its percentage will be measured with the total height.*Efficacy in aiding implant prosthetic rehabilitation*: The resonance frequency analysis (RFA) technique will be used to assess Implant Stability Quotient (ISQ) ranging from 1 (lowest stability) to 100 ISQ units (highest stability). The radiological analysis of the bone-implant area will be done and assessed in terms of bone implant contact, peri-implant radiolucency, and crestal bone loss. Soft tissue will be evaluated in terms of soft tissue recession, dehiscence, bleeding on probing and peri-implant exudation.*Quality of life of the patient*: The patient’s quality of life will be measured by the Liverpool Oral Rehabilitation Questionnaire-17 (LORQ-17), which assesses issues related to oral function, oro-facial appearance, and social interaction. Oral Health Impact Profile 14 (OHIP 14), which refers to prostheses and patient satisfaction with prostheses will be also rated using a 5-point Likert scale.

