## Appendix A

**Table d64e436:**

DATA CATEGORY	INFORMATION

Trial identification number	CTRI/2022/07/044291

Date of CTRI registration	25/07/2022

Sources of monetary or financial support	Biotechnology Industry Research Assistance Council (BIRAC), Govt. of India

Sponsor	Amrita Vishwa Vidyapeetham, Amrita Institute of Medical Sciences, Kochi, Govt. of India

Contact for public queries	[contact]

Contact for scientific queries	[contact]

Study type	Non-randomized Control Trial

Public title	Safety and efficacy evaluation of NANOTEX BONE graft along with fibula flap in reconstruction of the segmental mandibular defect – A Pilot Clinical Trial

Scientific title	A prospective, single-center, non-randomized pilot clinical study to evaluate the safety and efficacy of biodegradable NANOTEX BONE graft (Nanocomposite Fibrous Scaffold) along with fibula flap in reconstruction of segmental mandibular defect due to tumor resection or trauma

Countries of recruitment	India

Intervention	NANOTEX BONE graft

Date of the first patient enrolled	01/08/2022

Recruitment status	Started recruiting

Key inclusion criteria	Age- 18 to 65 years; Segmental mandibular defect due to benign tumor or trauma resection.

Key exclusion criteria	Patients indicated for radiotherapy before and after surgery; Mandibular ramus defects with open wounds; Active uncontrolled infection or malignancy; systemic diseases affecting surgical outcome

Primary outcome	To evaluate the safety of the NANOTEX BONE Graft in combination with fibula flap for bone augmentation

Secondary outcomes	To evaluate the efficacy of the NANOTEX BONE Graft in combination with fibula flap to regenerate new bone in aiding Titanium dental implant placement and integration

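### As stated, ISQ and undivided bone-implant readings do not separate integration in NANOTEX-derived bone from anchorage in the fibula beneath it

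*Protocol article*

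**What the plan says.** **The aim.** The Abstract says of NANOTEX that "further its ability to integrate with dental implants will be studied". The secondary objective in section 1.3 is to "evaluate the efficacy of the NANOTEX BONE Graft in bone regeneration when augmented on the fibula and Titanium dental implant integration". Appendix A words the secondary outcome differently, as the graft "in combination with fibula flap to regenerate new bone in aiding Titanium dental implant placement and integration".

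**The anatomy.** Section 2.8 describes an onlay: "the height of the fibula will be augmented by placing the scaffold over the fibula and fix with screws and a plate". As background on standard reconstruction, section 1.1 says that "Titanium dental implants will be placed to the fibula for dental rehabilitation", and it names reduced height as what restricts this. On implant choice, section 2.8 says only this: "The number and size of titanium dental implants will be planned based on bone gain".

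**The measures.** In section 2.10, under efficacy in aiding prosthetic rehabilitation, the "resonance frequency analysis (RFA) technique will be used to assess Implant Stability Quotient (ISQ") on a scale from 1 to 100. A radiological analysis of the bone around the implant covers bone-implant contact, peri-implant radiolucency and crestal bone loss. Under bone regeneration, the same section plans CBCT measurement of bone height, density, union and volume.

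**The comparator.** Section 2.1 describes a single-centre, non-randomised pilot. Appendix A labels the study type a non-randomised control trial, but no section describes a group, or a set of implants, in fibula without the graft.

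**The concern.** The question concerns the graft, but the readings concern the implant. If an implant passes through the augmented layer into living fibula, the fibula may hold it. ISQ cannot show which layer supplies the stability. Contact and radiolucency cannot show it either unless they are read by level. An implant anchored mainly in fibula, under a graft that formed little bone, could then count as integrated.

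At stake is the interpretation of a secondary efficacy result. Success of the standard fibula reconstruction could be reported as integration of NANOTEX-derived bone. The primary safety outcome is not affected.

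**Working it through.** The plan gives no figure for implant integration that could be reproduced. Its only calculation, the 10 subjects in section 2.6, rests on an adverse event rate and is not an input here. The check is therefore a comparison of passages, followed by an illustration on assumed lengths.

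**1. Can each planned measure separate graft from fibula?**

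| Measure (section 2.10) | What it reflects | Separates the layers as stated? |
|---|---|---|
| ISQ | Stability of the implant, one value | No |
| Bone-implant contact | Contact at the implant surface, level not stated | Only if read by level |
| Peri-implant radiolucency | Gap around the implant, level not stated | Only if read by level |
| Crestal bone loss | Change in marginal bone level | Partly: with an onlay, the crest should lie in augmented bone |
| CBCT height, density, union, volume | Whether new bone formed | Partly: shows bone, not its bond to titanium |

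Section 1.2 itself reports new bone formation and integration of that bone with titanium implants as distinct preclinical results. Evidence for the first is not evidence for the second.

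**2. Can change over time help?** Section 2.11 compares baseline with later findings. Section 2.9 places implants at 6 months, so no ISQ exists before then. A later rise could come from healing in the fibula alone.

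**3. Can a comparator help?** None is described, so there is no fibula-only value against which to judge the readings.

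**4. How large could the fibula's share be?** The article gives no implant length, implant depth or bone gain. Suppose an implant of length L starts at the top of the augmented layer and the bone gain is g. Then

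share in fibula = max(0, (L − g)/L).

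With assumed values only:

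| L (mm) | g = 2 mm | g = 6 mm | g = 10 mm |
|---|---|---|---|
| 8 | (8 − 2)/8 = 75% | (8 − 6)/8 = 25% | 0% |
| 10 | (10 − 2)/10 = 80% | (10 − 6)/10 = 40% | 0% |
| 12 | (12 − 2)/12 = 83% | (12 − 6)/12 = 50% | (12 − 10)/12 = 17% |

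The share runs from nil to dominant, depending on quantities that the article does not fix. Share of length is also not share of stability; it shows only that the question is open.

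**5. Is the share necessarily largest where the graft does worst?** Along each row it is, because L is held fixed. But section 2.8 sizes implants by bone gain. If length falls in step with gain, the share need not change: 12 mm with 6 mm gain and 8 mm with 4 mm gain both give 50%. The direction is plausible but not established.

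**The case against.** The strongest reply has four parts.

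- **Implant depth is inferred.** No section says how deep study implants go. The statement about implants in fibula is background, and the same section gives the fibula's low height as the reason for augmentation. This stands. That an implant reaches the fibula is a reasonable inference from the onlay geometry, not a stated fact.
- **The article condenses a fuller plan.** It refers to a clinical investigation plan (section 2.12) and a separate SAP (section 2.11), which may set the level at which contact is read. This stands for contact and radiolucency, on which the article is silent; it does not say that they are read over the whole implant. It does not rescue ISQ, which has no layer-specific form.
- **Other measures bear on the new bone.** A graft that formed little bone should show as poor CBCT bone gain, and crestal bone loss should concern the augmented zone. This stands as partial evidence. Neither measures contact along the augmented segment.
- **The registered outcome is the combination.** Appendix A, and the heading under which ISQ sits in section 2.10, fit a measure of the combined construct. This stands too, but the Abstract and section 1.3 do not carry that limit for integration.

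Two stronger readings are tempting. A reader might infer that the trial cannot show graft integration at all. The documents do not support that, because contact could be read by level on imaging already planned and two groups of measures already bear on the new bone. A reader might also infer that the ambiguity carries into the loading decision and the prosthesis outcomes. Section 2.8 makes loading depend on good integration with bone without naming ISQ, and no such effect is shown.

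**Conclusion.** The concern holds in a limited form. As section 2.10 stands, ISQ, bone-implant contact and peri-implant radiolucency do not distinguish integration in NANOTEX-derived bone from anchorage in fibula, and no fibula-only reference is described. A favourable result on them alone does not support the aim in the Abstract and section 1.3. Crestal bone loss and CBCT bone gain narrow the gap without closing it.

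The size is unknown. The 0% to 83% range rests wholly on assumed lengths and gains, and shows only that the fibula's part may be nil or dominant. The lack of a control group is the declared design of a pilot and is not itself the fault; it is why the readings need to be specific to the layer. The conclusion assumes that at least some implants extend into fibula and that the fuller plan does not already require readings by segment.

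**What to change.** Before the implant images are read, state in section 2.10, or in the fuller plan, that:

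1. for each implant, the length within the augmented layer and the length within fibula are recorded from the planned imaging, using the fibula and graft positions already set in the virtual surgical plan;
2. bone-implant contact and peri-implant radiolucency are read separately for the augmented segment, and that reading is the graft-integration outcome;
3. ISQ is reported as stability of the combined fibula-graft-implant construct, beside the share of implant length in augmented bone, and not alone as evidence of graft integration.

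If the segments cannot be read separately, limit the aim in the Abstract and section 1.3 to the graft in combination with the fibula flap, as in Appendix A.

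The cost is a few extra measurements per implant on imaging already planned, some endpoint wording, and a narrower integration claim. No extra patient or procedure is needed.

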### 2.11. Data analysis plan

The sponsor along with Clinical Research Organization (CRO) will conduct the statistical analysis through a separate Statistical Analysis Plan (SAP). In general, continuous data will be presented by descriptive statistics i.e. mean, standard deviation (SD), median, minimum and maximum values. To test the statistical significance between baseline and post findings, paired t-test for normal data or Wilcoxon -Signed rank test for skewed data will be used. Categorical data will be summarized using counts (N: Number of subjects per treatment group, n: number of subjects with non-missing values) and percentages. To test the statistical significance of the changes in the proportion of categorical variables between baseline and post-findings, McNemar’s Chi-Square test will be used.

### 2.12. Quality control

Sponsor/CRO shall ensure proper monitoring of this clinical study through trained clinical research associates or monitors appointed by them. To ensure that the study is conducted following the CIP, the Clinical Trial Agreement, and applicable regulatory and local requirements, the Sponsor/CRO representative or delegates will be allowed access to the subjects’ case histories (clinic and hospital records, and other source data/documentation) upon request. The consent form will be available for monitoring and auditing. The Principal Investigator and site personnel will provide the monitor (s) with complete access to primary source data (e.g., paper and electronic hospital/clinical charts, laboratory records), which support the CRF data and other documents regarding the conduct of the study. Monitoring visits may be scheduled periodically to ensure high degree of data quality.

## Appendix A

**Table d64e436:**

DATA CATEGORY	INFORMATION

Trial identification number	CTRI/2022/07/044291

Date of CTRI registration	25/07/2022

Sources of monetary or financial support	Biotechnology Industry Research Assistance Council (BIRAC), Govt. of India

Sponsor	Amrita Vishwa Vidyapeetham, Amrita Institute of Medical Sciences, Kochi, Govt. of India

Contact for public queries	[contact]

Contact for scientific queries	[contact]

Study type	Non-randomized Control Trial

Public title	Safety and efficacy evaluation of NANOTEX BONE graft along with fibula flap in reconstruction of the segmental mandibular defect – A Pilot Clinical Trial

Scientific title	A prospective, single-center, non-randomized pilot clinical study to evaluate the safety and efficacy of biodegradable NANOTEX BONE graft (Nanocomposite Fibrous Scaffold) along with fibula flap in reconstruction of segmental mandibular defect due to tumor resection or trauma

Countries of recruitment	India

Intervention	NANOTEX BONE graft

Date of the first patient enrolled	01/08/2022

Recruitment status	Started recruiting

Key inclusion criteria	Age- 18 to 65 years; Segmental mandibular defect due to benign tumor or trauma resection.

Key exclusion criteria	Patients indicated for radiotherapy before and after surgery; Mandibular ramus defects with open wounds; Active uncontrolled infection or malignancy; systemic diseases affecting surgical outcome

Primary outcome	To evaluate the safety of the NANOTEX BONE Graft in combination with fibula flap for bone augmentation

Secondary outcomes	To evaluate the efficacy of the NANOTEX BONE Graft in combination with fibula flap to regenerate new bone in aiding Titanium dental implant placement and integration
